**Abstract**

Currently, young adults are exposed to work and study overload and, therefore, often end up developing stress-related illnesses. Mindfulness-based stress reduction programs (MBSR) have been carried out in the most diverse contexts, being treated as possible therapies for depression, anxiety, chronic pain, and chronic stress. Originally created as an eight-week program, it is now being adapted for brief interventions leading to greater adherence to the activities and to the program itself. The relationship of the practices with improvement of attention on daily activities has been demonstrated. However, the interoceptive component that is directly trained as part of mindfulness-based practices, and it is related to well-being and greater capacity for self-regulation is not well understood. In this sense, the present study seeks to understand the relationship between brain activity, emotional regulation, attentional and interoceptive skills after a brief mindfulness-based intervention. To address this aim, blood and saliva cortisol levels will be assessed. Moreover, cognitive and attentional tasks will be performed in addition to evaluation of interoception, anxiety, stress and mindfulness as a trait and as a state.

**1. Introduction**

In the las decades, the literature has shown the use of new approaches with a mind-body integrative focus in order to prevent or treat illnesses that have increased with the lifestyle adopted in current societies, such as anxiety, depression and stress (ESCH et al. ., 2007; MARCHAND, 2012; UEBELACKER; BROUGHTON, 2016; WANG et al., 2014). Stress can be characterized as any disturbance to the body's homeostasis provided by exteroceptive stimuli (eg, predator smell, visual information) or interoceptive stimuli (blood volume, osmolarity) (ULRICH-LAI; HERMAN, 2009). In the social and psychological sphere, a survey carried out in the United States showed that the main triggering factors for stress are the economic situation, employment, family, and health status (APA, 2014). Stress is manifested in individuals of all ages, especially in young adults who are often subjected to study and work routines, in parallel, leading to a biopsychosocial overload.

The general adaptation syndrome or stress response was first described by Hans Selye in 1936 (Selye, 1936) and aims to maintain the physiological integrity of the organism. Therefore, this response is extremely necessary for survival if it is maintained at optimal levels, its absence or exacerbation being responsible for important physiological disorders and inappropriate responses to a specific demand (MCEWEN; WINFIELD, 2010). It is primarily mediated by the Hypothalamus-Pituitary-Adrenal (HPA) axis through a cascade of cellular events that lead to the release of hormones into the bloodstream. One of the main markers of HPA axis reactivity to stress is the hormone cortisol, which is released by the biological clock in a circadian rhythm and through stressful situations to the organism's homeostasis (HAUS, 2007; SELMAOUI; TOUITOU, 2003). This reactivity can be measured using various techniques, including investigation using blood plasma, urine, and saliva. From a stressful stimulus, there is activation of neurons located in the paraventricular nucleus (PVN) of the thalamus, which produce and secrete the corticotropic hormone releasing factor in the portal-pituitary system. Subsequently, there is the production and release, from adenohypophysis, of the adrenocorticotrophic hormone (ACTH) that, through the bloodstream, reaches the adrenal gland cortex, promoting the production and release of glucocorticoids, such as cortisol. Cortisol acts by negative feedback on the hypothalamus and pituitary in such a way that, when reaching high concentrations in the blood, it inhibits the release of factors that promote its production (SANDERS, 1983; SAPOLSKY; ROMERO; MUNCK, 2000; STRATAKIS; CHROUSOS, 1995; TSIGOS; CHROUSOS, 2002; ULRICH-LAI; HERMAN, 2009). In addition to the activation of the HPA axis, there is an important regulation of the autonomic nervous system (ANS) during the stress response, such as, for example, the change in cardiac activity, mediated mainly by the release of catecholamines, which also act on the PVN nucleus of the thalamus and limbic regions (GOLDSTEIN, 2003; KOPIN, 1995; ULRICH-LAI; HERMAN, 2009). In addition, neuromodulators such as BDNF (brain-derived neurotrophic factor) and the expression of its receptors are also affected in cases of acute or chronic stress, an effect observed in studies with rodents and humans (LICINIO; WONG, 2002; MURAKAMI et al., 2005; TAKAHASHI et al., 2000). BDNF is mainly related to synaptic plasticity and neurogenesis, and alterations in its release or in the expression of its receptors can cause deficits in important basic processes such as the acquisition of a new memory or development of psychiatric disorders (ALLEVA; SANTUCCI, 2001; BERTON et al. al., 2006; HORCH et al., 1999; MURAKAMI et al., 2005; TAKAHASHI et al., 2000). The brain's response to stressful stimuli (non-physical or psychogenic stimuli) is based on previous experience from the activation of previously established neural circuits or on innate programs of the organism. These reactions are usually processed in the forebrain, involving the limbic system and may occur in anticipation or in response to a stressful stimulus, for review see (ULRICH-LAI; HERMAN, 2009).

**Mindfulness-based programs**

The search for ways to reduce the impact of routine and social pressure on health led to the development of preventive and therapeutic alternatives for situations of stress. One is the use of systematized meditative practices over eight weeks known as the Mindfulness Based Stress Reduction program (MBSR).

Mindfulness-based programs began in a clinical setting in the 1970s through the development of a program for managing stress and chronic pain (KABAT-ZINN, 1990; KABAT-ZINN; LIPWORTH; BURNEY, 1985). Currently, there are several modalities of mindfulness-based programs aimed at specific pathologies or groups. Among the best known are MBSR, MBCT (Mindfulness based cognitive therapy) and MBRP (Mindfulness based relapse prevention). Overall, mindfulness-based stress reduction practices form a well-established training program over 8 (eight) weeks. In this program, activities are developed that use meditative practices as a tool aimed at refining the attention and self-awareness of the practitioner (KABAT-ZINN, 1990). What is cultivated in this practice is a present moment awareness, with openness, curiosity and a non-judgmental attitude, where the attentional focus is directed to the observation of the experience of thoughts, bodily sensations and emotions (HOLZEL et al., 2011; KABAT-ZINN, 1990).

Training effects have been demonstrated as efficient in the treatment of different diseases with important outcomes such as structural and functional changes of the central nervous system (CNS) and, consequently, in the expression of the individual's behavior. Disorders such as anxiety (KOCOVSKI et al., 2015), depression (HOFMANN et al., 2010), substance abuse (BOWEN et al., 2007, 2014) and eating disorders (GODSEY, 2013; O'REILLY et al., 2014) are among the most studied in the context of the application of mindfulness as a therapy. In addition, rehabilitation after breast cancer (HUANG et al., 2015; WÜRTZEN et al., 2015) and cases of chronic pain (BAWA et al., 2015; COUR; PETERSEN, 2015; KABAT-ZINN; LIPWORTH; BURNEY, 1985) also characterize a large part of the studies carried out in the last 30 years.

With the diversity of works found in the literature about the application of mindfulness-based programs, there are three main lines where the studies are concentrated: attention training, benefiting people with attention deficit hyperactivity disorder or similar condition (ZYLOWSKA DEBORAH ACKERMAN MAY H YANG JULIE L FUTRELL NANCY L HORTON T SIGI HALE; PATAKI; SMALLEY, 2008), better emotional regulation from the recognition of automatic modes of thoughts or feelings in people with depression (KUYKEN et al., 2015), and o development of self-knowledge and improved resilience in the face of stressful situations in people with some mental disorder (DAVIS; SETH KURZBAN, 2012).

MBSR (specifically aimed at reducing stress) has been widely studied in healthy individuals or with some disease and its effect has been demonstrated on the neuroendocrine axis with short and long-term interventions (BROWN; WEINSTEIN; CRESWELL, 2012; CHIESA; SERRETTI, 2009; CRESWELL et al., 2014; DECKRO et al., 2002; O'LEARY; O'NEILL; DOCKRAY, 2015)

Creswell et al. in 2014 demonstrated that a 3-day MBSR exercise practice improved participants' perception of stress when compared to a control group. In this study, participants underwent the social stress test (TSST - Trier Social Stress Test) after the interventions and it was found that people who have a more pronounced mindfulness trait before the intervention have lower neuroendocrine axis reactivity to acute stress. However, compared to the control group, the group undergoing mindfulness practice had, in general, an increase in the level of salivary cortisol (CRESWELL et al., 2014). In fact, the mindfulness trait seems to influence cortisol levels and the individual's relationship with negative emotions, with those with a lower trait being more prone to emotional dysfunctions and those with a higher trait showing better adaptation to a stressful stimulus (BROWN; WEINSTEIN; CRESWELL, 2012; DAUBENMIER et al., 2014).

In a 6-week mindfulness-based program in students, was observed lower levels of perceived stress, anxiety, and depression (DECKRO et al., 2002).

In a systematic review about the relationship between mindfulness practice and cortisol levels, the authors report the impossibility of reaching a common conclusion about the results found. This is due to lack of randomization or methodological problems found in the studies. (O’LEARY; O’NEILL; DOCKRAY, 2015).

**Mindfulness, emotional regulation, attentional and interoceptive ability**

Recently, some studies have demonstrated structural and functional changes observed in the brain of experienced meditators (HASENKAMP; BARSALOU, 2012; HÖLZEL et al., 2007; KANG et al., 2013; KILPATRICK et al., 2011; KURTH et al., 2015; LAZAR; LAZAR et al., 2005). Generally, brain areas that exhibit differentiated activity in meditative practitioners consist of cortical and subcortical regions involved in the limbic system. They are the prefrontal cortex, a region related to metacognition, planning and judgment; hippocampus, an area related to memory processing; anterior and orbitofrontal cingulate cortex, areas related to the perception of the “self”, attentional and emotional regulation; insula, region related to interoception; amygdala, region related to emotional processing, in addition to areas involved with inter-hemispheric communication such as the corpus callosum and the superior longitudinal fasciculus for review, see (TANG; HÖLZEL; POSNER, 2015b). Interestingly, regions of the limbic system seem to be related to the regulation of the paraventricular nucleus of the hypothalamus, an important site that constitutes the HPA axis. Thus, changes in activation of limbic regions can lead to physiological differences in the response to some stressful event (ULRICH-LAI; HERMAN, 2009).

One of the main components of mindfulness-based activities is attention regulation (BISHOP et al., 2004). From the implementation of these practices, changes have been observed in the subcomponents of the attentional system, such as orienting, alerting and monitoring in different contexts (MALINOWSKI, 2013; TANG; HÖLZEL; POSNER, 2015b).

Mindfulness practices involve focused attention, when it uses a fixed focus during its execution and is present mainly at the beginning of practices, and open monitoring, when the individual develops the ability to naturally move their attention between the elements of the experience (MALINOWSKI, 2013). Overall, studies demonstrate better performance on attentional tests in experienced meditators and this is correlated with cortical areas directly involved in the attention process. (MALINOWSKI, 2013; TANG; HÖLZEL; POSNER, 2015b). Jha et al. in 2007 demonstrated better performance in the Attention network test (ANT) of individuals who underwent an 8-week MBSR and individuals who participated in a month-long retreat and performed focused attention practices and open monitoring, corroborating other contemporary studies to this one (JHA; KROMPINGER; BAIME, 2007; TANG et al., 2007).

Regarding the attentional component, using electroencephalography (EEG), Fan et al. demonstrated an increase in the alpha wave potential in frontoparietal regions during an attention test after the practice of mindfulness-based exercises. The increase in the potential of these waves, in this region, seems to be associated with a better cognitive performance, reflected in a shorter reaction time to the stimulus, in addition to a smaller number of errors throughout the task (FAN et al., 2014). In addition, a reduction in frontal alpha asymmetry has also been reported after an 8-week mindfulness program. This result seems to be related to a better emotional regulation capacity involving greater well-being and less reactivity to emotionally negative situations (ZHOU; LIU, 2016).

Interoception or interoceptive ability can be described as the individual's ability to become aware of the signals originated from the body itself (FARB et al., 2015). This ability has been related to greater well-being and better self-regulation, considering that it is necessary for the perception of internal events that are important for survival (FARB et al., 2015; LIOTTI et al., 2001). In a recent study, an interesting change was observed in the self-report of personal aspects such as attention to the body after 3 months of contemplative practices (BORNEMANN et al., 2015). Along with changes in self-report, the change in interoceptive attention was measured through an instrument developed for this purpose called Multidimensional Assessment of Interoceptive Awareness (MEHLING et al., 2012).

Farb et al. in 2013 demonstrated that mindfulness practice leads to greater cortical activity in regions related to interoception, such as the anterior portion of the insula (FARB; SEGAL; ANDERSON, 2013). Considering that most mindfulness practices use attention focused on internal events, the interoceptive component as a benefit of the practices must be considered.

However, there is no study in the literature that demonstrates the effects of a brief mindfulness-based intervention on cortical activity, affective measures and interoceptive ability.

**2. Objectives**

General:

• Assess the impact of a brief training on the stress response, interoception and well-being on healthy individuals.

Specific:

• Verify the relationship between mindfulness trait and hypothalamic-pituitary-adrenal axis reactivity.

• Analyze the neuroendocrine response to a stress event after a brief mindfulness-based intervention.

• Assess the impact of mindfulness practice (3 days) on the attention system, autonomic nervous system, and interoceptive ability.

• Check the influence of the practice on self-report measures of stress, anxiety, and affect

• Assess participants' electroencephalographic activity before and after the proposed intervention, during a sustained attention test, an interoception test, and during the stress test.

**3. Materials and Methods**

Participants

Fifty young adults of both sexes, aged between 18-35 years will be recruited through wide dissemination on the campus of the Federal University of Rio Grande do Norte-UFRN. The sample size was determined with G * Power of the F test family (RM-ANOVA with intra-between interaction), considering a moderate to high effect size (f = 0.3) at α = 0.05 and 80% of power, as well as 60% correlation between repeated measures and considering loss of participants during the study being necessary at least 40 participants to attend these parameters.

Participants will be interviewed in advance and will complete a series of questionnaires to verify their eligibility for the study. Upon being elected to the study, they will be randomized into two groups proposed in this study.

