**Statistical analysis**

Initially, Kolgomorov-Smirnov normality tests will be applied to determine if the data obey a normal distribution. Once this prerequisite is met, Student's t test (parametric variables) or Mann Whitney U test (non-parametric variables) will be applied to detect the occurrence of significant differences within group and ANOVA to evaluate between groups differences. Spearman's correlation test will also be applied to test the occurrence of correlations between variables (anxiety, affect, stress and mindfulness, trait and state).

An exploratory and confirmatory factor analysis will be performed to verify the domains and association between the factors existing in the questionnaires. The internal consistency of the factors will be verified using Crombach's Alpha and only saturation values ​​greater than 0.4 for the eigenvalues ​​will be computed for the item's participation in the investigated domain.

For the analysis of plasmatic and behavioral markers, correlation tests and multivariate analysis will be used.

For all tests, the significance level (p value) less than or equal to 0.05 will be considered.

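### The stated minimum of 40 does not follow from the protocol's own sample-size inputs, and the interaction test it was sized on is not named in the analysis section

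*Protocol*

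**What the plan says.** The Participants paragraph of section 3 (Materials and Methods) opens with the recruitment target: "Fifty young adults of both sexes, aged between 18-35 years will be recruited". The calculation was done in G*Power, and the test chosen there is given as "RM-ANOVA with intra-between interaction". The assumed correlation from one measurement to the next is 0.6. The effect size and error rates appear as "considering a moderate to high effect size (f = 0.3) at α = 0.05 and 80% of power". The conclusion drawn from these inputs is "considering loss of participants during the study being necessary at least 40 participants to attend these parameters". Participants are randomised to two groups.

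The paragraph does not state the number of repeated measurements, the loss rate, the sphericity setting, the effect-size option or the outcome. Elsewhere the protocol has outcomes with different numbers of measurements: the sustained attention task is done in two sessions, and saliva is sampled four times around the stress test.

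The Statistical analysis section plans a t test or Mann-Whitney test for differences within group and "ANOVA to evaluate between groups differences". It does not name a group-by-time interaction. It also does not say whether the ANOVA is one-way on post-intervention values or uses repeated measures.

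**The concern.** The paragraph names the software, the test and nearly all the inputs, so a reader should be able to recover 40. Under the default settings the answer is about half that or less.

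Two further problems sit behind the number. In the named test, f is defined on the interaction, so f = 0.3 corresponds to a much larger group difference than the same f in an ordinary comparison of two means. And the test used for sizing is not the one named for the analysis.

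What is at stake is the meaning of the 80% claim. A reader will take it that the trial has 80% power for a mid-sized difference between mindfulness and colouring, and will read a null result accordingly. The text supports that only if test, effect and number are tied together, and they are not.

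**Working it through.** **Inputs.** From section 3: f = 0.3, α = 0.05, power 80%, ρ = 0.6, k = 2 groups. Assumed: 1:1 allocation and sphericity (ε = 1) unless noted. The number of measurements m is not stated, so 2 to 4 are shown.

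**1. The protocol's own figure.** G*Power default for the within-between interaction, noncentral F:

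λ = N·f²·m/(1−ρ), df1 = (k−1)(m−1), df2 = (N−k)(m−1).

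For m = 2, λ = N × 0.09 × 2/0.4 = 0.45N.

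| m | λ | Smallest even N for 80% | Power at that N | Power at N = 40 |
|---|---|---|---|---|
| 2 | 0.45N | 20 | 81.0% | 98.5% |
| 3 | 0.675N | 16 | 80.2% | 99.7% |
| 4 | 0.90N | 14 | 81.5% | over 99.9% |

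None gives 40.

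**2. Allowing for loss.** Starting from 20, a loss of 10%, 20% or 30% gives 23, 25 or 29. Reaching 40 needs 1 − 20/40 = 50% loss for m = 2, 1 − 16/40 = 60% for m = 3 and 1 − 14/40 = 65% for m = 4. If 40 is instead the number before loss, with 50 recruited to cover it (1 − 40/50 = 20%), the mismatch is 40 against 20 with no inflation to explain it.

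**3. Unstated settings that come near 40.** With m = 4 and lower-bound ε = 1/3, λ = 0.30N and N = 30; 30/(1 − 0.25) = 40 after 25% loss. With m = 4 and an alternative effect-size option with λ = f²·N·(m−1) = 0.27N, N = 42. That option takes no correlation, whereas the protocol says 0.6 was used.

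**4. What f = 0.3 means in the named test.** For two groups and two measurements, a difference in change of δ gives interaction cell effects of ±δ/4. So f = δ/(4σ) and δ = 4 × 0.3 = 1.2 SD. The SD of a change score is √(2(1 − 0.6)) = 0.894 SD, so on the change scale the standardised difference is 1.2/0.894 = 1.34.

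**5. If f = 0.3 is read as a group difference.** In a one-way comparison of two equal groups, f = d/2, so f = 0.3 is 0.6 SD. Power for 0.6 SD:

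| Between-group test | λ | N = 40 | N = 50 |
|---|---|---|---|
| One-way ANOVA, post-intervention only | 0.09N | 46% | 55% |
| Change score (equivalent to the interaction, m = 2) | 0.45N/4 = 0.1125N | 54% | 64% |
| Repeated-measures group factor, m = 2 | 0.18N/1.6 = 0.1125N | 54% | 64% |
| Repeated-measures group factor, m = 4 | 0.36N/2.8 = 0.129N | 60% | 70% |

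The numbers needed for 80% are 90 (one-way) and 72 and 64 (group factor, m = 2 and m = 4).

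**6. The same underlying effect under a one-way test.** With equal baselines, a 1.2 SD difference in change is a 1.2 SD post-intervention difference, or one-way f = 0.6. One-way ANOVA power is then 95.9% at 40 and 98.6% at 50.

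**The case against.** The strongest defence has three parts.

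First, the error is on the safe side. For the test named in section 3, 40 participants exceed the stated power, and recruitment is 50. This stands: a reader who infers that 40 is too few for the stated calculation would be wrong.

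Second, a reader might infer that the planned ANOVA has only 46% to 55% power at the protocol's own effect. The documents do not support that. Those figures belong to a 0.6 SD difference, whereas the interaction f = 0.3 is 1.2 SD in change, for which even a one-way post-intervention test has over 95% power. They also presume a one-way, post-only ANOVA, which the analysis section does not specify. That section's ANOVA could be meant as the repeated-measures model of section 3, and its exact form may properly be settled in a statistical analysis plan that is not shown.

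Third, settings exist that yield roughly 40, so a definite slip in arithmetic is not proven. This also stands in part. But those settings need a sphericity correction plus a loss rate, or an effect-size option that does not use the correlation the protocol reports. None is disclosed.

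What remains is that 40 is not obtainable from what is written, that the effect-size label does not fit the test, and that the two sections do not name the same test.

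**Conclusion.** The point holds in limited form. From the stated inputs and the G*Power default, the required number is 20, 16 or 14 for two, three or four measurements, not 40; power at 40 is at least 98.5%. The excess is conservative for the named test, but only against a 1.2 SD difference in change (m = 2).

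If the intended target is a 0.6 SD group difference, none of the between-group ANOVA or change-score tests in the table reaches 80% with 40 or 50 participants; the range is 46% to 70%. The protocol does not say which target it means, so the trial cannot be called underpowered outright. Nor can the 80% be taken as established for a mid-sized effect.

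The results assume 1:1 allocation, sphericity and the default effect-size definition, except where another setting is named. The documents give no expected effect, so no judgement is made on whether 1.2 SD is plausible.

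**What to change.** Keep enrolment as it is and change the wording in two places.

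1. In section 3, replace the statement that links f = 0.3, 80% power and 40. Give the outcome, the number of measurements, the effect-size option, the sphericity setting, the assumed loss rate, and the target difference in SD units with its power at 40 and 50. If the two-measurement interaction is kept, 80% power corresponds to a difference in change of about 0.81 SD at 40 (f = 0.203, 4 × 0.203 = 0.81) and about 0.72 SD at 50; power for 0.6 SD is 54% and 64%.

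2. In the Statistical analysis section, name the same between-group test: either the group-by-time interaction used for sizing, or another test reported with its own power.

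Baseline-adjusted ANCOVA would do better (λ = 0.09N/(1 − 0.36); 64%/74% for 0.6 SD, about 0.73/0.65 SD detectable at 80%). Neither section mentions it, so these figures should be used only if ANCOVA is also adopted in the analysis section. A 20% loss rate should likewise be written only if the sponsor confirms it, because it is merely implied by 50 and 40.

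The cost is one paragraph and one sentence, and a power statement that may look less favourable. No extra participants are needed.
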